### Safety considerations and adverse events

All measurements are non-invasive and place the subject at no risk other than those that normally may occur during walking. For some of the patients, in particular those who were not practicing any kind of physical exercise prior to the intervention; there is a slight possibility that subjects might feel some muscle soreness and fatigue after training. To prevent excessive fatigue, subjects will be encouraged to take breaks as needed throughout all study procedures. In addition, the study was designed for gradual increases in intensity which will help to increase endurance and build muscle strength. Virtual reality may cause cyber sickness, a sensation similar to motion sickness. This phenomenon is, however, very rare and is related to highly immersive technology. The proposed study will use a 2D projection to deliver the VR simulation which decreases the risk of developing cyber sickness.

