**Methods/Design:**

Three hundred older adults with a history of falls will be recruited to participate in this study. This will include older adults (n=100), patients with mild cognitive impairment (n=100), and patients with Parkinson’s disease (n=100). These three sub-groups will be recruited in order to evaluate the effects of the intervention in people with a range of motor and cognitive deficits. Subjects will be randomly assigned to the intervention group (treadmill training with virtual reality) or to the active-control group (treadmill training without virtual reality). Each person will participate in a training program set in an outpatient setting 3 times per week for 6 weeks. Assessments will take place before, after, and 1 month and 6 months after the completion of the training. A falls calendar will be kept by each participant for 6 months after completing the training to assess fall incidence (i.e., the number of falls, multiple falls and falls rate). In addition, we will measure gait under usual and dual task conditions, balance, community mobility, health related quality of life, user satisfaction and cognitive function.

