## Background

Gait impairments and falls are ubiquitous among older adults and patients with common neurological diseases. Approximately 30% of community-dwelling adults over the age of 65 fall at least once a year [1,2]. In persons with Parkinson’s disease (PD), mild cognitive impairment (MCI) or dementia, falls are even more frequent with annual incidence rising to 60–80% [2,3]. The consequences of these falls may be severe, leading to institutionalization, loss of functional independence, disability, fear of falling, depression and social isolation [4].

Most falls occur during walking [5,6] and, not surprisingly, gait impairment has been associated with an increased risk of falls [7,8]. Gait abnormalities in elderly fallers and patients with PD include reduced gait speed, stride length, and increased stride symmetry [9]. Fear of falling, cautious gait [10,11], gait unsteadiness, or dysrhythmicity of stepping have also been recognized as mediators of fall risk [12-15].

There is a growing body of research that specifically links the cognitive sub-domains of attention and executive function (EF) to gait alterations and fall risk [15-21]. EF apparently plays a critical role in the regulation of gait especially under challenging conditions where decisions need to be made in real-time [22]. Walking while avoiding obstacles and walking while simultaneously performing another task, i.e., dual tasking (DT), place greater demands on cognitive resources such as divided attention and executive control, judgment, and reasoning, compared to “single task” walking [23-25]. EF scores and dual tasking gait performance have been associated with fall history and have been shown to predict future falls, even over several years of follow-up [17,21,26]. Although there is no universal agreement, many studies in patients with PD have reported that EF and dual tasking gait abilities are associated with fall risk [27-29] and attention-deficits predict future falls in patients with PD [30]. This may explain why falls occur so frequently among older adults, and even more so in patients with PD and patients with MCI. We suggest that these three groups share cognitive deficits that contribute to and exacerbate their fall risk. MCI patients are cognitively impaired, by definition. As much as 60% of patients who receive the diagnosis of PD already have cognitive deficits [31,32], and many older adults suffer from age-associated decline in cognitive function.

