### Sample size calculation

The primary outcome measure is fall incidence rates during the 6 month post-training follow-up period. The sample size estimate is based on extrapolations from our pilot studies [49] and other related promising pilot work (e.g., Rosenblat et al. [54], Pai et al. [55] and, Weerdesteyn et al. [56]). Power was set at 80%, alpha was set at 5% and we accounted for drop out rate of 20%. Using a relatively conservative estimate, we assume that the control group fall incidence rate, after intervention, will be three falls per year. If we consider a 40% reduction for the treatment group relative to this, then, during the 6 month monitoring of falls incidence, a total of 166 subjects would be required for 80% power (83 in each group) to detect differences between the two treatment groups assuming non-inferiority with moderate correlations among covariates (R-squared = 0.50). A much smaller sample is needed to detect between group differences for the secondary outcomes. For example, with 22 subjects in the intervention and control arms, we will have 90% power to detect an intervention effect (assuming Cohen’s f for ANOVA of 0.21), in dual tasking gait speed. To enhance our ability to examine the effects of the intervention on fall incidence within the three sub-groups (seniors, PD, MCI), we will aim to recruit 100 subjects per group, for a total of 300 subjects.

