### Intervention

All interventions will be delivered by therapists trained in the standard protocols across centres in the consortium countries. Consistent with the motor learning literature and the pilot studies [49,52], all subjects will be trained 3 times a week for 6 weeks, each session will last approximately 45 minutes.

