### Assessment protocol

A repeated measures design will be employed with assessments performed 1 week pre-training, post-training, and at 1 month and 6 months post intervention (Table 1). A trained assessor in each centre, not involved in training and blinded to group allocation, will perform all assessments. Each participant will be assessed at about the same time of day to avoid variability of performance due to any circadian rhythms or medication intake cycle.

**Table 1 T1:** Assessment of outcome measures across the protocol

	**Category**	**Outcome measures**	**Pre training**	**Post training**	**One month follow up**	**Six month follow up**
Primary outcome measure	Falls	Fall frequency				x
Secondary outcome measures	Gait	Gait speed	x	x	x	x
		Gait variability	x	x	x	x
		2 MWT	x	x	x	x
	Balance and mobility	FSST	x	x	x	x
		SPPB	x	x	x	x
		mini-BEST	x	x	x	x
		Community ambulation	x	x	x	
	Cognitive function	MoCA	x			
		TMT	x	x	x	x
		Mindstreams tests of cogntive function	x	x		x
		Verbal Fluency	x	x	x	x
	Healthy Related Quality of Life	SF-36	x	x	x	x
		FES-I	x	x	x	x
	User satisfaction and views	User satisfaction Questionnaire		x		

2MWT- 2 Minute Walk Test, FSST-Four Square Step Test, SPPB- Short Physical Performance Battery, mini-BEST- The mini-Balance Evaluation Systems Test, MOCA- Montreal Cognitive Assessment, TMT- Trail Making Test, FES-I- Fall Efficacy Scale International.

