### Outcome measures

#### Primary outcome measures

The primary outcome measure of the study is fall rate. Participants will keep a falls calendar for 6 months post intervention. Consistent with the recommendations of the Prevention of Falls Network Europe (ProFaNE), a fall will be defined as “an unexpected event in which the participant comes to rest on the ground, floor or lower level”. Each time the participant falls he/she will tick the date on the calendar. These calendars will be returned to the researchers every two weeks in a pre-addressed envelope or using an online electronic calendar. Periodic contact by the research staff with each participant will be used to maximize compliance with the fall calendars.

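### The falls calendar opens only after training, so falls in the 6 training weeks cannot count against the claimed fall reduction

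*Protocol article*

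**What the plan says.** The protocol article fixes the fall window in four places, and they agree.

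- Abstract, Methods/Design: "A falls calendar will be kept by each participant for 6 months after completing the training to assess fall incidence".
- Sample size calculation: "The primary outcome measure is fall incidence rates during the 6 month post-training follow-up period".
- Primary outcome measures: "Participants will keep a falls calendar for 6 months post intervention".
- Table 1 (Assessment protocol) marks fall frequency at the six-month visit only.

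Randomization follows consent and comes before training (Recruitment and randomization procedure). Under Intervention, "all subjects will be trained 3 times a week for 6 weeks, each session will last approximately 45 minutes". The Assessment protocol has "assessments performed 1 week pre-training, post-training, and at 1 month and 6 months post intervention", so no scheduled assessment lies within the training weeks.

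The hypothesis at the end of the Background is that TT+VR, compared with TT alone, lowers the incidence and the risk of falls. It sets no time window.

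Safety considerations and adverse events says that the measurements "place the subject at no risk other than those that normally may occur during walking". It then names muscle soreness and fatigue as possible after training, and adds: "Virtual reality may cause cyber sickness, a sensation similar to motion sickness".

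**The concern.** In a falls trial, a fall is both the efficacy event and a foreseeable harm. Everyone enrolled has fallen at least twice in the previous 6 months (Common inclusion criteria). The Background states that "Most falls occur during walking" and lists obstacle crossing among the causes of falls. Training becomes harder week by week and is meant to change how people walk and behave. A temporary rise in falls while people adapt is plausible, though nothing in the article shows that it happens.

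A participant can complete all 18 sessions, fall several times at home during those weeks, and still add nothing to the fall rate. A conclusion that TT+VR reduces falls would then describe only the period after exposure, while the hypothesis reads as covering the whole course. Even without any harm, the post-training ratio need not equal the ratio from the start of training.

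**Working it through.** **Inputs from the article**
- Control rate after the intervention: 3 falls per year. Planned reduction: 40%, a rate ratio of 0.60 (Sample size calculation).
- Entry criterion: at least 2 falls in 6 months, which is at least 4 per year.
- Training lasts 6 weeks and the calendar 6 months, taken as 26 weeks.
- Planned total: 300.

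**Assumptions**
- Equal allocation, 150 per arm.
- A training-period control rate of 3 or 4 per year. The article gives 3 only for the time after the intervention. People selected for recent falls may regress towards a lower rate, so 4 is not a floor.
- Training-period rate ratios of 0.6, 1.0, 1.5 and 2.0, chosen for illustration.

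**Step 1. The plan's own rates.** Over 6 months the control arm has 3 × 26/52 = 1.5 falls per person and TT+VR has 0.6 × 1.5 = 0.9. These rates fit the stated total of 166. A Poisson comparison with one-sided alpha of 5%, 80% power, R-squared of 0.50 and no allowance for drop-out gives 2 × (1.645 + 0.842)² × (1/1.5 + 1/0.9) / (ln 0.6)² / (1 − 0.50) = 168.5, within 3% of 166. The present point does not depend on that figure.

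**Step 2. Falls outside the window.**
- At 3 per year: 3 × 6/52 = 0.346 per person, and × 150 = 52 per arm.
- At 4 per year: 4 × 6/52 = 0.462 per person, and × 150 = 69 per arm.
- Share of time from start of training to end of follow-up: 6/(6 + 26) = 18.75%.

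**Step 3. Rate ratio from the start of training.** With e the control falls per person in training and q the training-period rate ratio, the ratio is (0.9 + e × q)/(1.5 + e).

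| q (assumed) | 3 per year | 4 per year |
|---|---|---|
| 0.6 | 0.60 | 0.60 |
| 1.0 | 1.246/1.846 = 0.675 | 1.362/1.962 = 0.694 |
| 1.5 | 1.419/1.846 = 0.769 | 1.592/1.962 = 0.812 |
| 2.0 | 1.592/1.846 = 0.863 | 1.823/1.962 = 0.929 |

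The post-training ratio is 0.60 in every row. The two ratios agree only if TT+VR already has its full effect from the first week.

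**Step 4. What would cancel the benefit.** The assumed gain is 1.5 − 0.9 = 0.6 falls per person. It is cancelled when e × (q − 1) = 0.6, that is, q = 1 + 0.6/0.346 = 2.73 at 3 per year, or 1 + 0.6/0.462 = 2.30 at 4 per year.

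**Step 5. How much of the period is supervised.** Eighteen sessions of 45 minutes make 13.5 hours. Six weeks have 6 × 7 × 24 = 1,008 hours, so sessions cover about 1.3% of clock time. Their share of walking time is larger but is not given.

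**The case against.** The strongest defence is that the window is declared and consistent. A post-training rate is a legitimate primary outcome, and reporting 0.60 for it is reporting exactly what was planned. That stands, and it is why the primary outcome should not change. It does not remove the gap between that window and a hypothesis without one.

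A second defence is that training is protected. The article provides a safety harness in the TT+VR section, has trained therapists deliver all sessions, and ties progression to the participant's performance. This lowers the chance of injury in a session. It does not reach falls between sessions, which is where nearly all of the time is spent.

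Third, the size of any harm is assumed. This is correct: the article offers no evidence for a 1.5-fold or 2-fold excess, and doubled falls would still leave a net benefit.

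A reader might also draw three stronger inferences that the article does not support.

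- *That the safety section calls the training no riskier than walking.* The sentence is about the measurements. The same section goes on to name training risks and ways to limit them.
- *That soreness, fatigue and cyber sickness are recorded nowhere.* The article does not describe such recording, but a condensed article commonly leaves adverse-event procedures to the full protocol, which is not shown. The SF-36, given at the post-training visit, also covers bodily pain and energy/fatigue, although it is not an adverse-event form.
- *That early harm could not be seen at all.* For the same reason, the text supports only the narrower statement that training-period falls do not enter the fall rate as defined.

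**Conclusion.** The point holds for falls, and it rests on a stated rule rather than on silence: fall collection begins after training. About 0.35 to 0.46 falls per person, or 52 to 69 per arm of 150, would lie outside the outcome, over 19% of the time from start of training to end of follow-up. If the post-training ratio is 0.60 and the training-period control rate is 3 per year, the ratio from the start of training is about 0.68 with no training effect and about 0.77 to 0.86 with a 1.5- to 2-fold excess. At 4 per year the corresponding values are 0.69 and 0.81 to 0.93. These figures rest on the assumed training-period rates, the assumed excesses and equal allocation.

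The likely consequence is dilution that goes unseen in the fall rate. It would be wrong to read this as a reversal of the benefit, which would need a 2.3- to 2.7-fold excess of falls during training. The primary outcome is not invalid. This is a worthwhile and inexpensive improvement.

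**What to change.** 1. Issue the existing falls calendar at the start of training, with the same definition of a fall and the same two-weekly return.
2. Keep the six-month post-training rate as the primary outcome. The sample size is unaffected.
3. Report falls in weeks 1 to 6 by arm as a safety outcome.
4. Add the fall rate from start of training to month 6 as a supporting analysis.

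The cost is six more weeks of calendars, or 6/2 = 3 further returns per participant, with no extra visit. Staff already see participants three times a week. Because therapists know the allocation, reminders and collection must be identical in both arms.

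The comparison for weeks 1 to 6 will be imprecise. With 52 falls in each arm, a simple Poisson 95% interval extends by a factor of exp(1.96 × √(2/52)) = 1.47 either side of the ratio, and more with overdispersion or drop-out. It should be given as an estimate with its interval, and a non-significant difference should not be read as evidence of no harm.

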## Discussion

The aim of this study is to establish a practical and feasible solution for enhancing mobility, preventing falls and reducing disability among diverse groups of older adults using a unique intervention that combines treadmill training and virtual reality. What sets this project apart from previous work in this field is that the study simultaneously addresses both motor and cognitive function and their interactions that are key to falls using a large, RCT study design, with an active comparison control for assessing efficacy. Training is provided in a virtual environment that implicitly challenges, teaches, and enhances visual scanning, planning, DT abilities and obstacle negotiation. The additional training goals that aim to enhance the cognitive aspects of mobility have not yet been integrated into common practice and are one of the important added features of the proposed intervention. The unique training program takes onboard all aspects of motor learning in that it probes retention as well as transfer of training to real-world activities to maximize resilient effects.

In a sense, this study also addresses the concepts and concerns raised by Mahoney et al. [48]. The proposed training is intensive, focuses on the key impairment and becomes progressively more rigorous. The training and protocol were designed to meet the needs of a diverse group of older adults including those with cognitive deficits and motor impairment due to neurodegeneration. The intervention maximizes motor learning in order to induce a behavioural change. Moreover, training in the computer-controlled virtual environment makes the therapy and protocol standardized and reproducible.

The training protocol that is at the basis of this study was developed based on recently established guidelines on complex interventions in geriatrics [82-87]. The proposed protocol is based on the needs of the three groups who share a high risk of falls, in part due to cognitive deficits. Focus groups and questionnaires have been used to refine the intervention. Feasibility of using such an intervention was assessed and pilot studies were carried out. Further, the outcome measures are validated and selected to evaluate the effects of the intervention on falls and the motor cognitive interactions that contribute to fall risk. This process enables us to confidently advance into a large randomized controlled trial to explore efficacy in comparison to an active training control group.

Evidence on the efficacy of fall prevention in geriatrics is not yet ideal and large randomized control trials are needed. To promote motor learning required for safe ambulation, fall prevention interventions should include motor and cognitive aspects relating to falls, task-specific and generalized training, with the intervention centred around the user’s needs. The proposed intervention set out to bridge all these needs. The knowledge that will be generated by the results of this study are likely to inform new models of care that combine technology, mobility training, and cognitive remediation to reduce risk of falls and enhance mobility even in a chronic disease profile.

## Conclusions

This randomized controlled trial will demonstrate the extent to which an intervention that combines treadmill training augmented by virtual reality reduces fall risk, improves mobility and enhances cognitive function in a diverse group of older adults. In addition, the comparison to an active control group that undergoes treadmill training without the added virtual reality will provide evidence as to the added value of an intervention that addresses motor cognitive interactions as an integrated unit.
